#### Exclusion criteria

2.2.5

(1)Cardiogenic shock.(2)Severe heart failure (New York Heart Association classiﬁcation stages II–IV, or left ventricular ejection fraction ≤ 50%), or comorbid with severe valvular disease.(3)Severe liver or kidney dysfunction (serum alanine aminotransferase of at least double the normal upper limit and/or serum creatinine ≥ 265 μmol/L).(4)Patients with other vascular diseases, such as cerebrovascular disease, arteriosclerosis obliterans of the lower limbs or diabetes nephropathy.(5)Patients with active bleeding or severe hematopoietic system disease.(6)Patients with malignant tumors who are undergoing chemotherapy or radiotherapy who have not been clinically cured, or those who have been treated with special drugs for malignant tumors, or with life expectancy under 3 years.(7)Taken antibiotics within the previous 2 weeks.(8)Pregnant (or preparing to become pregnant) women, lactating women.(9)Have participated in, or are participating in, other clinical trials within the past 3 months.(10)The researcher determined that the participant was unable to finish the study or adhere to its requirements.

### Recruitment process

2.3

The research will include participants from both the outpatient and inpatient departments of the Guangdong Provincial Hospital of Traditional Chinese Medicine. Subjects who meet the eligibility criteria and provide informed consent will advance to a screening phase, while those who do not fulfill these requirements will be excluded prior to randomization. Principal investigators and attending physicians will jointly conduct eligibility assessment for enrolled participants based on specific inclusion/exclusion criteria. Registered participants will then be allocated through an online system for intervention and follow-up phases of the experiment. Ineligible individuals' demographic data, as well as any reasons for non-participation, will also be documented alongside strict confidentiality measures.

### Randomization and allocation concealment

2.4

The randomization process will employ a block randomization method. 98 patients will be randomly allocated into two groups at a ratio of 1:1 using block randomization. Each block will consist of 49 cases with random sequence arrangements within the blocks. We plan to use the PROC PLAN procedure in SAS V9.4 for this study. The results of both the randomization and the allocation procedures were conducted by researchers from the Clinical Research Methodology Team at Guangdong Provincial Hospital of Traditional Chinese Medicine. The random assignment procedure was registered with the TCM Clinical Research Methodology Team at Guangdong Provincial Hospital of Traditional Chinese Medicine. Random assignment results will be generated and released via a centralized randomization management system. Researchers will log into an online randomization system to apply for randomization and receive the randomization results.

### Blinding

2.5

This trial will be conducted in a double-blind manner, ensuring that neither the participants nor the research staff are aware of the group assignments. The Jiangyin Tianjiang Pharmaceutical Co., Ltd. (Jiangyin, China) will produce both the QSHTD and the placebo granules. The placebo will be designed to closely resemble the QSHTD in all aspects, such as color and flavor. All medications will adhere to the standards set by the National Drug Manufacturing Code of China. The blinding process and the maintenance of the blind will be handled by the TCM Clinical Research Methodology Team at Guangdong Provincial Hospital of Traditional Chinese Medicine. An emergency letter for each drug code will be created during the randomization and blinding process, and it will be securely sealed according to the corresponding drug group. If a serious adverse event (SAE) occurs or if urgent medical care is required, the principal investigator can use the online randomization system to request unblinding. When unblinding becomes inevitable, the participant will be excluded from the study, and the investigator must inform the examiner of the cause within 24 h. If unblinding is essential, the individual will be removed from the research, and the investigator must convey the reasons to the examiner within a 24-hour period.

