#### Secondary outcomes

2.7.2

(1) Canadian Cardiovascular Society Classification (24); (2) Seattle Angina Questionnaire (24); (3) TCM symptom evaluation; (4) MACE incidence rate, including all-cause mortality, nonfatal myocardial infarction, stroke, target vessel revascularization and stent thrombosis events.

Table 2 delineates the precise collection times for the outcome measures.

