### Safety assessment

2.8

Our team will meticulously document the exact timing, intensity, duration, interventions applied, and potential outcomes of all adverse incidents. For each documented incident, the investigator will also assess the connection between the adverse events and the medications under study. In line with ICH guidelines, SAEs will be classified as any occurrences that could lead to hospitalization, inability to work, birth defects, or fatalities (25). The investigator will notify the ethics committee of any SAE in 24 h.

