### Data analysis and managament

2.10

Data analysis will be performed using SAS 9.2 (SAS Institute Inc., USA) according to a pre-established statistical plan. The evaluation of effectiveness will adhere to the intention-to-treat principle. Quantitative data will be analyzed using methods such as ANOVA. Categorical data will be evaluated with chi-square tests and Fisher's exact test, while non-parametric rank sum tests and CMH chi-square tests will be used for ordinal data. The significance level will be set at *α* = 0.05, and a *P*-value below 0.05 will indicate a statistically significant difference. Descriptive statistics will summarize the baseline characteristics of the two groups. For continuous variables that are normally distributed or have an unknown distribution, *T*-tests or Mann–Whitney *U*-tests will be employed. To address missing data, appropriate imputation strategies will be used to minimize potential bias. This will involve multiple imputation techniques, allowing us to create several complete datasets by estimating missing values based on observed data trends. Proper handling of data is crucial for maintaining the precision, reliability, and traceability of clinical trial information, as stipulated by the Technical Guidelines for Clinical Trial Data Management (27) and the Good Clinical Practice standards (28).

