### Participant safety

2.12

Physicians participating in clinical trials must provide subjects with detailed information about the clinical trial, so that they can comprehend and voluntarily sign an informed consent form before the clinical trial commences. Participants are free to exit the trial at any point and for any cause; signing the informed consent document and meeting the eligibility criteria will not impact their future medical care. Although individuals have the freedom to exit the study whenever they wish and for any reason, it is advisable to refrain from doing so unless there is a significant necessity. Additionally, measures should be undertaken to complete as much follow-up as possible. This will enable the evaluation of its efficacy and safety.

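### The rule that unblinded participants leave the study is not reconciled with intention-to-treat and loses data for reasons linked to outcome

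*Protocol article*

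**What the plan says.** Section 2.5 (Blinding) gives the trigger: "If a serious adverse event (SAE) occurs or if urgent medical care is required, the principal investigator can use the online randomization system to request" (what is requested is a code break). It then states the consequence twice: "When unblinding becomes inevitable, the participant will be excluded from the study", and "If unblinding is essential, the individual will be removed from the research". Neither sentence makes an exception. The section does not say whether assessments continue or whether the participant's data are analysed.

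Four other places bear on this:

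- Section 2.10 sets the analysis principle: "The evaluation of effectiveness will adhere to the intention-to-treat principle". For missing data it adds: "This will involve multiple imputation techniques, allowing us to create several complete datasets by estimating missing values based on observed data trends".
- Section 2.12, in a paragraph on participants who choose to leave, says that "measures should be undertaken to complete as much follow-up as possible", so that efficacy and safety can be evaluated.
- Section 2.8 defines the trigger: "SAEs will be classified as any occurrences that could lead to hospitalization, inability to work, birth defects, or fatalities".
- Section 2.7.2 lists as a secondary outcome "MACE incidence rate, including all-cause mortality, nonfatal myocardial infarction, stroke, target vessel revascularization and stent thrombosis events".

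**The concern.** Whether a code is broken depends on what happens to the participant after randomisation, and the named occasions are serious events. Deaths, and MACE components that lead to hospitalisation, are serious adverse events under section 2.8 and endpoint events under section 2.7.2. A rule that removes participants after a code break therefore selects on something close to the outcome.

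If this selection differs between arms, those who remain are no longer the groups that randomisation created. The MBF comparison, the later symptom scores, MACE and the safety comparison could all be affected. An analysis plan cannot recover assessments that were not made because the protocol told sites to remove the participant.

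**Working it through.** **1. The two readings of section 2.5.**

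| Reading of the rule | Against section 2.10 (intention-to-treat) | Data lost |
|---|---|---|
| Removed from the analysis | Direct contradiction: a randomised participant is dropped because of a later event | All of that participant's effectiveness data |
| Withdrawn from follow-up, kept in the analysis set | Compatible in form, with missing values imputed | Everything scheduled after the code break |

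The article does not say which reading is meant.

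**2. What the second reading loses.** Table 2 schedules RTMPE at baseline and week 12 only. CCSC, SAQ and TCM symptom scores are collected at baseline, week 12 and week 24. A participant removed before week 12 therefore has a baseline MBF and no later one, and no later symptom score. Events and adverse events scheduled for collection up to week 24 are lost from the point of removal.

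**3. Whether imputation repairs it.** For such a participant, imputation would draw the week-12 MBF largely from people with similar baseline values who stayed in. That is adequate only if, given the observed data, the removed participants would have changed as the others did. Participants selected because of a serious event are the ones for whom this is least credible.

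**4. The planned effect and sample size (section 2.9), reproduced.**

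- Difference: 0.97 − 0.52 = 0.45 dB/s.
- Pooled SD: √((0.72² + 0.68²)/2) = √0.4904 = 0.7003 dB/s.
- n per arm, two-sided α = 0.05, power 0.80: 2 × (1.96 + 0.8416)² × 0.4904 / 0.45² = 38.02, rounded up to 39. The noncentral t calculation gives 80.0% power at 39.
- Dropout: 39 / (1 − 0.20) = 48.75, so 49 per arm and 98 in total.

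The stated figures hold.

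**5. Bias in MBF, assumed illustration.** Let a fraction p of an arm be removed, and let their mean change be d dB/s worse than that of those who remain. The mean of those who remain then exceeds the full arm mean by p × d. The bias in the difference is

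p(experimental) × d(experimental) − p(control) × d(control).

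- One arm only, p = 0.10 (about 5 of 49), d = 0.7 (about one SD): 0.10 × 0.7 = 0.07 dB/s, and 0.07 / 0.45 = 15.6%.
- If that arm is the experimental one, a true 0.45 appears as 0.45 + 0.07 = 0.52. If it is the control arm, it appears as 0.45 − 0.07 = 0.38.
- Both arms, same p and same d: 0.07 − 0.07 = 0.

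The values of p and d are assumptions. The article gives no code-break rate.

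**6. Power.** If removals come on top of the 20% dropout allowance, t-test power falls from 80.0% at 39 evaluable per arm to 77.8% at 37 and 74.2% at 34. A few removals cost little power. The dropout allowance protects precision and does nothing about selection.

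**The case against.** The strongest defence is that leaving the study is not the same as leaving the analysis. Section 2.10 commits to intention-to-treat and provides for imputation, and the definitions of analysis sets may stand in documents not shown. This stands as far as it goes: a flat contradiction with intention-to-treat exists on one reading only. It does not rescue the rule, because the other reading still loses data selectively.

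Three further limits also stand:

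- A serious adverse event does not by itself remove anyone. The investigator may request unblinding, and removal follows only if the code is broken. Such cases may be few, and the Discussion concedes that the trial may be unable to observe major cardiac events.
- Some participants with a serious event, and all who die before week 12, would have no week-12 RTMPE under any rule. The loss caused by this rule is smaller than the total loss in such patients.
- The follow-up sentence in section 2.12 is written about voluntary exit. It shows that the protocol values continued follow-up, but it does not directly contradict section 2.5.

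Two stronger inferences are tempting and not supported. A reader might infer that a MACE that leads to a code break disappears from the count. The event precedes the code break, however. Section 2.8 requires all adverse incidents to be documented, Table 2 collects endpoint events at every visit, and nothing in section 2.5 says that recorded events are discarded. A reader might also infer that safety follow-up of the triggering event stops. Section 2.8 requires the duration and outcomes of all adverse incidents to be recorded and makes no exception for unblinded participants. What is at risk is what happens to that participant afterwards.

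**Conclusion.** The rule is wrong as written. It is explicit and stated twice, it is tied to serious events, and it is not reconciled with section 2.10. On the harsher reading it contradicts intention-to-treat. On the milder reading it creates missing data related to outcome, which the stated imputation would not correct.

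The size of the bias cannot be computed from the article. The 0.07 dB/s shift rests on three assumptions: 10% removed, from one arm only, with a deficit of 0.7 dB/s. It scales in proportion to the first and third, and it vanishes in the difference when removal and deficit are equal in both arms. The conclusion itself does not depend on these values, and the planned sample size is unaffected.

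**What to change.** Replace both exclusion sentences in section 2.5, and reconcile them with sections 2.10 and 2.12, by stating that:

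- an unblinded participant stays in the intention-to-treat and safety analyses in the arm as randomised;
- all events before and after the code break are counted;
- follow-up to week 24 continues where consent and the treating physician allow;
- the unblinding is recorded as a deviation, with its date and reason;
- those who read the outcome assessments stay blinded.

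Decisions on study medication, and on whether a stress test is appropriate for a given participant, remain matters of clinical judgement and should be kept separate from study follow-up.

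The cost is a change of wording. The small downside is that a few participants are followed with their allocation known to the treating physician.

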### Intervention

2.6

Referring to the 2018 ESC Guidelines for Coronary Artery Revascularization, all subjects will be given antiplatelet drugs, statin lipid-lowering drugs, nitrate esters, anticoagulants, and *β* receptor blocker (23). After a subject is enrolled, their previous standard treatment plan will be maintained. Any modifications to the treatment, the patient's status, or the drug's quantity or variety should be documented in details.

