#### Inclusion criteria

2.2.4

(1)Age range is from 18 to 80 years old.(2)PCI performed within the previous 2 years and rSS ≥ 2 points; or PCI was performed at least 2 years before and coronary angiography was performed within the previous 2 years with rSS ≥ 2 points; or PCI was performed at least 2 years before and there is untreated or unsuccessfully treated chronic total occlusion.(3)Meet the 2017 clinical diagnostic criteria for phlegm-damp syndrome in CHD, as well as the dampness syndrome diagnostic criteria.(4)Agree to undergo adenosine stress real-time myocardial perfusion echocardiography (RTMPE).(5)A signed consent form is required.

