#### Concomitant medication during the trial

2.6.3

(1)Use of any other traditional Chinese patent medicines or decoctions will be prohibited during the test.(2)Any patients entering the screening period must discontinue the usage of any long-acting nitrate drugs (such as long-acting nitroglycerin) or any other anti-angina treatments. However, they may continue using a beta-blocker and/or calcium channel blocker if they are taking one.(3)Throughout the study period, patients will be prohibited from adding or using any of the following medications, in addition to maintaining their original medication: beta blockers, calcium antagonists, nitrate drugs (except for the use of short-acting nitroglycerin for angina attacks).(4)Any medications or treatments necessary for managing coexisting conditions should be documented, including the drug name (or other treatment name), dosage, frequency of use, and duration. This data is crucial for both analysis and reporting.

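### Section 2.6 gives five background drug classes to all subjects and then keeps each subject on existing treatment; the two rules differ for anyone not already taking a listed class, and section 2.6.3 does not settle it.

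*Protocol article*

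**What the plan says.** Section 2.6 of the protocol article sets the background treatment for both arms in three sentences.

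- The first refers to a 2018 European revascularization guideline and states that "all subjects will be given antiplatelet drugs, statin lipid-lowering drugs, nitrate esters, anticoagulants, and *β* receptor blocker (23".
- The second states: "After a subject is enrolled, their previous standard treatment plan will be maintained".
- The third concerns records: "Any modifications to the treatment, the patient's status, or the drug's quantity or variety should be documented in details".

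Section 2.6.3 (Concomitant medication during the trial) adds restrictions.

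- Item 2, on screening: "Any patients entering the screening period must discontinue the usage of any long-acting nitrate drugs". Other anti-angina treatments stop as well, but "they may continue using a beta-blocker and/or calcium channel blocker if they are taking one".
- Item 3, for the whole study: "patients will be prohibited from adding or using any of the following medications, in addition to maintaining their original medication: beta blockers, calcium antagonists, nitrate". Short-acting nitroglycerin for attacks is exempt.
- Item 4 requires treatment of coexisting conditions to be recorded.

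The inclusion criteria (section 2.2.4) turn on age, revascularization history, TCM syndrome, agreement to the stress echocardiogram and consent. The first route into the revascularization criterion, for instance, is "PCI performed within the previous 2 years and rSS ≥ 2 points". None of them requires a particular background drug. The exclusion criterion that concerns bleeding directly is "Patients with active bleeding or severe hematopoietic system disease".

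**The concern.** The first two sentences of section 2.6 are both written as rules, and they agree only for a patient who already takes every class on the list. For anyone else, one sentence starts a drug at enrolment and the other leaves treatment unchanged. A treating physician cannot follow both.

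The anticoagulant shows what is at stake. Read literally, the first sentence puts every participant on an antiplatelet and an anticoagulant together, whether or not the patient was on both before. That would carry a bleeding risk that comes from the background regimen and not from the study decoction. If some physicians follow one sentence and some the other, background care also varies between patients for reasons unrelated to their condition. Safety is one of the trial's two stated aims, so the treatment on which adverse events are observed should be fixed by a single rule.

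**Working it through.** No figure in the article depends on this point, so the check is a comparison of texts, class by class, for a patient **not** taking the class at entry.

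| Class | 2.6, first sentence | 2.6, second sentence | 2.6.3 |
|---|---|---|---|
| Antiplatelet | given | not added | additions not barred |
| Anticoagulant | given | not added | additions not barred |
| Statin | given | not added | additions not barred |
| Nitrate | given | not added | may not be added, except short-acting nitroglycerin for attacks |
| Beta blocker | given | not added | may not be added |

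**Step 1: within section 2.6.** Columns two and three disagree in all five rows. The third sentence of section 2.6 does not help: it asks for modifications to be recorded, but does not say whether enrolment itself should cause one.

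**Step 2: does section 2.6.3 settle it?** In part. Item 3 speaks of patients maintaining their original medication, and nothing in that phrase confines it to anti-anginal drugs. It therefore leans towards the maintain reading. But the prohibition it introduces names only beta blockers, calcium antagonists and nitrates. No item of section 2.6.3 names antiplatelets, anticoagulants or statins. For the first three rows the question stays open.

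**Step 3: the last two rows.** Here section 2.6.3 contradicts the first sentence of section 2.6 outright. Nitrates are given to everyone in one place; in the other, long-acting nitrates are stopped at screening and nitrates may not be added. Beta blockers are given to everyone in one place; in the other, they continue only in patients already taking one. This is the more direct conflict, and it arises from the same sentence.

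**Step 4: do the eligibility criteria remove the problem?** No. The inclusion criteria do not require any of the five classes, so patients without one or more of them can enrol. Active bleeding, severe hematopoietic disease, severe liver or kidney dysfunction and cerebrovascular disease are excluded, and the investigator may exclude others as unable to finish or adhere. These criteria narrow who enters; they do not say which background drugs an enrolled patient is given.

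**Step 5: does it reach the sample size?** No. Section 2.9 uses MBF changes of 0.52 (SD 0.72) and 0.97 (SD 0.68), α = 0.05 and power 80%.

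- Difference: 0.97 − 0.52 = 0.45.
- Common SD: √((0.72² + 0.68²)/2) = 0.700.
- Taking α as two-sided (the article does not say), a two-sample t-test needs 39.0, so 39 per group, as stated.
- Dropout: 39/(1 − 0.20) = 48.75, rounded up to 49 per group and 98 in total, as stated.

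None of these inputs depends on which sentence of section 2.6 is followed.

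**The case against.** The best defence is that the first sentence only describes standard care. It opens by referring to a guideline and lists drug classes, while the second sentence is tied to enrolment and so reads as the operating rule. Section 2.6.3 repeats the idea of maintaining original medication, so that idea appears twice and the given-to-all wording once. This is probably what the authors meant, but the text does not say so. The first sentence applies to all subjects without qualification, although the authors do write conditionally elsewhere, as in section 2.6.3 on beta blockers. If the list is only descriptive, the wording still needs to show it.

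A second defence is that an article condenses the full protocol. That would answer a complaint about missing detail. It does not answer two adjacent published sentences that state different rules.

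A third is that the sentence must be rewritten anyway because of the nitrate and beta-blocker conflict. That is right, and one amendment should deal with both. A repair limited to anti-anginal drugs would leave the other three classes open.

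A reader might go further and infer that the safety comparison between arms is biased. The documents do not support this. The background rule is the same in both arms of a 1:1 randomized, double-blind trial, so a physician's choice between the sentences should not follow the allocation. Table 2 also schedules adverse events, serious adverse events, complications and medication at baseline and at weeks 4, 8, 12 and 24, so there is a place to record bleeding and drug changes at every visit.

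**Conclusion.** The contradiction is real and modest in size. Section 2.6 contains two rules that differ for any patient not already taking all five classes. Section 2.6.3 leaves three of the classes unresolved (antiplatelet, anticoagulant, statin) and contradicts the first rule for the other two (nitrate, beta blocker). The consequence is for participant safety and for uniform background care in both arms. It is not a between-arm bias, and the primary MBF analysis and the sample size are unaffected.

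It would be tempting to say how many of the 98 patients are affected. The article gives no share of patients on any of these drugs at entry, so any count would only restate an assumption. Nor does the text show that anticoagulants will in fact be started in patients not taking them; it shows only that one sentence, read literally, calls for it. Effects on MACE are also hard to argue here, since the Discussion accepts that such events may not be observed in 24 weeks.

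The conclusion assumes that the published wording matches the full protocol. If the full protocol already states one rule per class, only the article needs correcting.

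**What to change.** Reconcile the sentences of section 2.6 with each other and with section 2.6.3. For each class (antiplatelet, anticoagulant, statin, nitrate, beta blocker, calcium antagonist), one rule should state whether screening or enrolment changes the patient's existing treatment. If the guideline list is meant only to describe usual care, the text should say that. Which clinical rule applies is for the investigators to set; this review takes no position on it.

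The cost is a wording amendment, with ethics committee approval before it takes effect, as section 2.11 requires for any protocol change. No new data are needed, because medication is already recorded at every visit in Table 2, and the sample size and primary analysis stay as they are.

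### Sections 2.6 and 2.6.3 give conflicting rules for background anti-anginal therapy, so the anti-anginal part of standard care in both arms is undetermined

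*Protocol article*

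**What the plan says.** Section 2.6 (Intervention) sets the background for everyone: "all subjects will be given antiplatelet drugs, statin lipid-lowering drugs, nitrate esters, anticoagulants", with a beta receptor blocker closing the list. It then states: "After a subject is enrolled, their previous standard treatment plan will be maintained". Changes to treatment are to be documented.

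Section 2.6.3 (Concomitant medication during the trial) sets three further rules that bear on the same drugs:

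- On entering screening, patients "must discontinue the usage of any long-acting nitrate drugs (such as long-acting nitroglycerin) or any other anti-angina treatments".
- There is an exception: "they may continue using a beta-blocker and/or calcium channel blocker if they are taking one".
- For the whole study, "patients will be prohibited from adding or using any of the following medications, in addition to maintaining their original medication". The classes named are beta-blockers, calcium antagonists and nitrates, with short-acting nitroglycerin for attacks exempted.

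Sections 2.6.1 and 2.6.2 define the arms as standard care plus QSHTD and standard care plus placebo. Neither says which of these rules standard care follows. Table 2 places consent, the random number, RTMPE, CCSC and SAQ in one baseline column covering weeks −2 to 0.

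**The concern.** Both arms are built on standard care, so the effect to be estimated is that of QSHTD on top of a particular background. For anti-anginal drugs, the document prints two rules for that background which cannot both be followed in some patients.

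These drugs act on angina, and two secondary outcomes, the Canadian Cardiovascular Society class and the Seattle Angina Questionnaire, measure angina and its consequences. The primary outcome, change in MBF under adenosine stress, may also be affected. If patients are handled under different readings, their results vary for reasons unrelated to the study drug, and the report cannot say clearly what QSHTD was added to. Section 2.11 requires deviations to be documented, but a deviation cannot be judged against two incompatible rules. The most immediate consequence is practical: treating physicians have instructions that they cannot all carry out.

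**Working it through.** The question is one of consistency in the text, so the check is to apply each section to each kind of patient at entry.

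| Patient at entry | Section 2.6 | Section 2.6.3 | Result |
|---|---|---|---|
| Not on a beta-blocker | To be given one | Allowed only if already taken; adding one is barred | Direct contradiction |
| On a beta-blocker | Given; prior plan kept | May continue | Consistent |
| On a calcium channel blocker | Prior plan kept | May continue | Consistent |
| On a long-acting nitrate | Nitrate esters given; prior plan kept | Stopped on entering screening | Conflict, unless the prior plan means the plan after screening and nitrate esters means short-acting use only |
| On another anti-anginal drug | Prior plan kept | Stopped on entering screening | Conflict, unless the prior plan means the plan after screening |
| On no nitrate | Nitrate esters given | Adding nitrates barred, except short-acting nitroglycerin for attacks | Conflict, unless nitrate esters means short-acting use only |

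Three observations follow.

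1. The first row has no reconciling reading. It does not depend on what the previous plan or nitrate esters means.
2. The nitrate and other-drug rows can be reconciled only by supplying meanings that the text does not give.
3. Section 2.6.3 is itself unclear. One rule withdraws a long-acting nitrate, while the next speaks of keeping the original medication and, in the same sentence, bars using the class. Whether original means before or after the screening withdrawal is not said.

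The only related figures are in section 2.9, and they are not in question. The planned difference is 0.97 − 0.52 = 0.45 dB/s and the pooled SD is √((0.72² + 0.68²)/2) = √0.4904 = 0.700. A two-sided t-test at α = 0.05 with 80% power needs 38.9996 per group, rounded up to 39. Then 39/0.80 = 48.75, rounded up to 49 per group and 98 in total, as stated. What the conflict leaves open is whether the control-arm value of 0.52 ± 0.72 dB/s, taken from a conventionally treated group, describes this trial's own background. The document gives no figure for how MBF, SAQ or angina class would differ between the two readings.

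**The case against.** The strongest defence is that the two sections describe a sequence. Section 2.6.3 governs entry to screening, and the sentence on keeping the prior plan governs the time after enrolment. Withdraw certain drugs first, then hold the regimen fixed: that is coherent. Nitrate esters in section 2.6 need not mean long-acting ones, and short-acting nitroglycerin stays allowed. For patients already on a beta-blocker or calcium channel blocker the sections agree. All of this is fair and it narrows the point. But the sequence is not stated, and it does not help the patient who enters without a beta-blocker.

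Three stronger readings are tempting, and the document does not support them.

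- *The comparator as a whole is undefined.* It is not. The control is standard care plus matching placebo, and the antiplatelet, statin and anticoagulant components are stated without conflict.
- *The randomised comparison is biased, for example by a withdrawal effect inside the 12-week change.* The same rules apply to both arms of a randomised, double-blind trial, so such an effect falls equally on both in expectation.
- *Power falls by a definite amount.* Any such figure needs an assumed split of patients between the readings and an assumed shift in MBF. The document supports neither, and in a single-centre trial with joint eligibility assessment an even split is not an obvious expectation.

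The order of assessments within the baseline window is also a detail that a condensed article may leave to the full protocol. It is not counted here as a separate error. The recording of treatment changes is already covered by sections 2.6 and 2.6.3 and by the medication row of Table 2.

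**Conclusion.** The contradiction is real and is visible in the printed text. It is certain for patients not on a beta-blocker at entry. It holds for patients on a long-acting nitrate or another anti-anginal drug unless unstated meanings are supplied. The anti-anginal component of standard care is therefore undetermined in both arms.

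The harm lies in incompatible instructions to clinicians, an unclear background against which to interpret the result, and possible extra variability in angina class, SAQ and perhaps MBF. Its size cannot be estimated, because the document gives neither the share of patients affected nor the effect of these drugs on the outcomes. The conclusion rests on the wording of the two sections alone. It needs correcting because it determines what patients receive and because the text cannot be followed as written.

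**What to change.** Reconcile sections 2.6 and 2.6.3 into one background anti-anginal rule. It should cover patients who are and are not taking each class at entry, and should say whether the previous plan means the regimen before or after screening. Which rule to adopt is a clinical decision for the sponsor, and no view on it is offered here.

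As a supporting step, state that the baseline RTMPE, SAQ and CCSC already planned for weeks −2 to 0 are taken once that rule is in force and before randomisation, so that the 12-week change is measured from a settled background.

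The cost is amendment wording, ethics committee approval as section 2.11 requires, and a fixed order for assessments that are already scheduled. No new procedure, visit or patient is needed, and the sample size is unchanged.
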